## 2.6 Intervention

This study aims to reduce social anxiety in preschoolers by tailoring an MM intervention that targets parents to alleviate social anxiety levels in their children. Collaborating with parents and caregivers will result in a more effective and tailored solution that resonates with their practical needs and experiences. Their input can lead to a more feasible and impactful study design, refining eligibility criteria, recruitment, and data collection procedures. A participatory co-design was conducted in order to strengthen the quality and outcomes of this research. The intervention will be identical in both countries, with the only difference being the language used for the programme. All other elements, such as the structure, content, delivery methods, and materials of the MM training programme, will remain uniform across both locations.

The MM training programme will consist of three online sessions, each lasting one hour and conducted over three consecutive weeks. The training sessions will be conducted through Zoom, and participants will receive a unique link to access the platform securely. This training is designed to equip caregivers with strategies for attuned, mentalizing caregiving, focusing on enhancing their ability to understand and respond to their child's emotional and mental states.

The first session will introduce the concept of mind-mindedness and its importance in caregiving. It will include psychoeducation on the development of social anxiety in children and how caregiver responsiveness plays a crucial role. Caregivers will also be introduced to basic emotion coaching techniques, which will be explored in more depth in the second session. The second session will focus on teaching and practising these emotion coaching techniques, helping caregivers recognise, validate, and guide their children's emotions in a supportive manner. The final session will deepen the caregivers' understanding through reflective discussions and advanced role-play scenarios that address common challenges in caregiving with socially anxious children.

All three sessions will include video examples demonstrating effective and ineffective approaches, as well as role-play exercises where caregivers can practice these techniques with guided feedback. The role-plays will be led by trained child psychologists. They will give immediate feedback and answer questions to ensure that caregivers are effectively practising mentalizing caregiving. Throughout the training, caregivers will receive support materials and reminders to track their progress and reflections. Participation will be tracked through attendance records and the completion of reflection activities to make sure that participants are following the programme guidelines.

## 2.7 Control group

The peer support (control) group will access a private online group for the exchange of experiences and coping strategies related to the child's anxiety, without direct MM training. Control group participants will access a secure online forum, where they can post entries and interact through comments, called Padlet. No Zoom sessions will be used, and no structured training or psychoeducation will be delivered in this group.

The comprehensive set of measures includes assessments of MM, child anxiety scales, and evaluations of attachment and theory of mind. Measures of MM will be coded from caregiver descriptions of the child using the MM Coding Manual 2.2 (64). Child anxiety will be assessed with the Spence Children’s Anxiety Scale (65). Attachment will be measured using the Attachment Insecurity Screening Inventory (67). Theory of mind will utilise the Theory of Mind Task Battery (69). The three-day MM training programme incorporates psychoeducation, role-play exercises, and practical sessions, while the peer support (control) group serves as an active control condition.

Fig 1-2. RCT design

## 2.8 Statistical methods

### 2.*8*.1 Sample Size and Power

A power analysis was conducted in advance using G*Power 3.1 to determine the necessary sample size for linear regression models with two predictors: group assignment and baseline score. Assuming a medium effect size (f² = 0.15), an alpha level of 0.05, and a power of 0.80, the analysis indicated that a minimum sample size of 89 participants is required. To account for an expected attrition rate of approximately 10–15%, we plan to recruit 100 participants, with 50 participants in each group. These participants will be evenly distributed between the United Kingdom and Iran. This target is deemed feasible and suitable for an early-phase efficacy trial. The sample is designed to provide sufficient power for testing the primary effects of the intervention using regression-based methods, while maintaining enough power for within-group analyses.

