Various interventions have been conducted by researchers to explore the link between child development and caregivers' mind-related comments. Schacht et al.(2017) reported that a single-session video-feedback intervention was effective in reducing non-attuned comments (30). This intervention proved to be beneficial for mother-infant interactions even up to the second year of life. Another study conducted by Larkin et al. developed the BabyMind app, which was successful in increasing MM among adolescent mothers (29). Walker's (2012) research emphasised the importance of MM in preschool clinical interventions (52).

This paper proposes an RCT of MM training for caregivers of socially anxious preschoolers. This study emphasises the need to adapt interventions for diverse populations. Research indicates culture shapes caregiving approaches, parenting behaviours, and attachment styles (53, 54). Some studies reveal differences in MM across Western and Eastern cultures. For instance, British parents exhibit higher MM towards children compared to Chinese parents, but both show positive links between MM and child theory of mind (55). Research indicates that Western mothers engage in more mental state talk with children than Eastern mothers (56). Collectivist values in Eastern cultures prioritise hierarchy and conformity versus individuality in the West impacts manifestations of MM in parent-child interactions (57, 58). According to some research, traditional gender norms can also affect father-daughter relationships and emotional attunement in Persian families specifically (59, 60). For instance, in a study comparing parenting practices in the UK and India, they found notable differences: UK mothers made more mind-minded comments, while Indian mothers issued more instructions and positive comments, reflecting cultural priorities (61). These differences highlight the influence of cultural contexts on parenting practices. Recognising and understanding these variations can guide the development of interventions sensitive to cultural contexts, ultimately promoting healthier outcomes for children worldwide(53, 62).

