## 2.2 Trial design

This study protocol outlines the design and methodology of a randomised controlled trial aimed at investigating whether MM training for caregivers can effectively reduce social anxiety symptoms in preschoolers by employing a cross-cultural approach involving caregivers from the UK and Iran. Participants will be randomly assigned to either the MM training intervention group or a peer support (control) group. Randomisation will be carried out separately for each country's sample. Stratified random sampling will ensure a balanced allocation within each country's participants.

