## 2.5 Procedure

Participant allocation will be carried out using a computer-generated randomisation sequence through Random Allocation Software 2.0, which will assign caregivers to either the mind-mindedness (MM) training intervention group (n=50) or the peer support control group (n=50). The randomisation will be stratified by country (UK and Iran) to maintain a balanced allocation within each cultural context (FIGURE

1).

Data collection will take place at three time points: baseline (T0), post-intervention (T1), and 3-month follow-up (T2). At each time point, data will be collected through validated caregiver-report measures (FIGURE

2). Mind-mindedness will be assessed using the Mind-Mindedness Coding Manual 2.2 (64), which offers a structured framework for coding caregivers' descriptions of their children. This method evaluates both the frequency and appropriateness of the mental-state language caregivers use when describing their child. It has been widely applied in developmental studies involving preschool-aged children. Child social anxiety symptoms will be measured using the Spence Children’s Anxiety Scale – Parent Version (SCAS-P)(65), while the scale was initially validated for children aged 6 to 12, it has also been effectively used in parent-report studies with younger children aged 4 to 6(66). Attachment security will be assessed using the Attachment Insecurity Screening Inventory (AISI) for Preschoolers (67). This caregiver-report tool is specifically designed for two age groups: children aged 2 to 5 years and 6 to 12 years old, which evaluates both anxious and avoidant attachment patterns. The AISI has demonstrated good construct validity and cross-cultural applicability, making it suitable for use in both the UK and Iranian populations.

The assessment of Theory of Mind (ToM) will be conducted using the Theory of Mind Task Battery (68) for evaluating the theory of mind. The battery has been validated for use with preschool children and demonstrates strong convergent validity with other socio-cognitive measures. All measures were selected based on their age appropriateness, prior validation within preschool populations, and their cross-cultural applicability.

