Additionally, demographic information (such as age, gender, socio-economic status, and cultural background) will be collected to describe the study population and control for potential confounding variables. Programme adherence will be monitored through attendance records and weekly caregiver reflections on their experiences.

The informed consent process will follow institutional guidelines, ensuring participants receive detailed study information in their preferred language (English or Persian). Participants will have opportunities to ask questions and will receive a clear explanation of their right to withdraw from the study. The Principal Investigator (PI) is responsible for obtaining informed consent from all potential trial participants.

To enhance engagement in the online format, participants will receive regular reminders via email and SMS before each session. The sessions will be interactive and will include breakout room role-plays and guided reflection activities. The control group will encourage informal peer support and provide a platform for them to share their experiences.

Comprehensive data protection measures will be implemented, including secure storage of consent forms and assessment data in encrypted, password-protected files. Unique participant identifiers will be assigned, and access will be restricted to authorised research personnel only. All data management procedures will comply with GDPR and local data protection regulations. The final dataset will be accessible only to the research team and will be stored according to Heriot-Watt University's data retention policy. This thorough approach to randomisation, data collection, and protection ensures both scientific validity and participant confidentiality throughout the study.

Figure 2-2."Participants’ Timeline"

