### 2.*8*.2 Primary Analysis

The primary analysis will evaluate the effectiveness of the mind-mindedness training in improving outcomes for both caregivers and children immediately after the intervention. We will use linear regression models for each outcome, which includes caregiver mind-mindedness, child social anxiety (using SCAS-P), attachment insecurity (AISI), caregivers’ MM, and the Theory of Mind (ToM Task Battery). Each model will compare the post-intervention scores (Time 1) between the intervention and control groups, while controlling for baseline values (Time 0). All analyses will adhere to intention-to-treat principles. The effects of the intervention will be assessed using linear regression models, comparing outcomes at post-intervention (T1) and follow-up (T2) to baseline (T0), while controlling for baseline scores. When applicable, multiple imputation with 20 datasets will be used to address any missing data. Effect sizes will be reported using standardised beta coefficients and 95% confidence intervals.

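### Randomisation is stratified by country, but the stated T1 and T2 models leave country out, so intervals may be wider and power lower than they need be

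*Protocol*

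**What the plan says.** On design, section 2.2 states: "Randomisation will be carried out separately for each" country's sample. Section 2.5 adds: "The randomisation will be stratified by country (UK and Iran) to maintain a balanced allocation within each cultural context". It names the allocation software but no block method.

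On analysis, section 2.8.1 bases the sample size on "linear regression models with two predictors: group assignment and baseline score". Section 2.8.2 describes the primary models in the same terms: "Each model will compare the post-intervention scores (Time 1) between the intervention and control groups, while controlling for baseline values (Time 0"). Sections 2.8.2 and 2.8.3 treat the three-month scores likewise, with baseline as the only named adjustment. The UK/Iran contrast appears once in section 2.8, in the moderation models of section 2.8.3, through interaction terms.

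Section 2.5 also says that demographic data, including cultural background, are collected partly to "control for potential confounding variables". No model in section 2.8 names such a covariate.

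**The concern.** A factor used to stratify randomisation normally belongs in the analysis model. Balancing the arms on country removes country differences from the treatment contrast. A model without country still counts those differences as residual noise, so the standard error does not credit the balance that the design achieved. If the within-country lists are not blocked, chance imbalance on country adds real noise to the estimate, which a country term would remove.

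In either case the trial would report wider intervals and have less power than its own data allow. With 100 recruits and a stated minimum of 89, that is a needless cost. It arises only if country predicts the T1 or T2 score after the T0 score is taken into account.

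**Working it through.** **The plan's own figure.** Inputs from section 2.8.1: two predictors, f² = 0.15, alpha 0.05, power 0.80, stated minimum N = 89. With a noncentral F (noncentrality f²·N, denominator df N − p − 1), the test of the group coefficient needs N = 55 and the joint test of both predictors needs N = 68. The stated 89 is not reproduced at power 0.80; it equals the single-coefficient N at power 0.95. That is a separate matter. What matters here is that adding country as a third predictor leaves the single-coefficient N at 55, and power at N = 89 is 0.951 with or without the extra term.

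**Formula under balance.** Let δ be the UK–Iran difference left after baseline adjustment, in residual SD. The protocol does not give δ, so the range 0 to 1.0 is an assumption. With equal countries and arms balanced within each, omitting country multiplies the residual variance by 1 + δ²/4. The standard error grows by the square root of that, and the true type I error is 2(1 − Φ(1.96·√(1 + δ²/4))). For δ = 0.5 the variance factor is 1 + 0.25/4 = 1.0625, the SE ratio is 1.031, and type I error is 2(1 − Φ(2.02)) = 4.3%.

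**Simulation check.** N = 88, baseline–outcome correlation 0.5 (assumed), 12,000 null replicates. The Monte Carlo error on a 5% rate is √(0.05 × 0.95/12,000) = 0.2 points. Type I error is for the model without country.

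| δ | SE ratio, formula | SE ratio, simulated, balanced | Type I, formula | Type I, simulated, balanced | Type I, simulated, unblocked |
|---|---|---|---|---|---|
| 0 | 1.000 | 1.000 | 5.0% | 4.86% | 5.19% |
| 0.2 | 1.005 | 1.006 | 4.9% | 5.06% | 5.03% |
| 0.5 | 1.031 | 1.031 | 4.3% | 4.45% | 4.96% |
| 0.8 | 1.077 | 1.079 | 3.5% | 3.63% | 4.92% |
| 1.0 | 1.118 | 1.121 | 2.8% | 2.68% | 5.25% |

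**Which mechanism applies.** At δ = 0.8 with balanced arms, the actual spread of the estimate is 0.2168 without country and 0.2166 with it, so no precision is lost. The reported SE without country is 0.2304 against 0.2135 with it, so it is overstated. With simple randomisation within country, the spread rises to 0.2313 without country against 0.2164 with it, and the reported SE of 0.2316 is honest. The interval is wider in both cases (ratios 1.079 and 1.071).

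**Power (5,000 replicates), without → with country, %.** For equal arms f² = d²/4, so f² = 0.15 is a group difference of 2√0.15 = 0.775 residual SD, the residual being that of the model with country. The 0.6 SD column is an assumed smaller effect, chosen because power is then near 80% at N = 88.

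| δ | f² = 0.15, balanced | f² = 0.15, unblocked | 0.6 SD, balanced | 0.6 SD, unblocked |
|---|---|---|---|---|
| 0 | 94.2 → 94.2 | 94.4 → 94.3 | 78.2 → 78.1 | 79.1 → 78.5 |
| 0.2 | 93.8 → 93.9 | 94.1 → 94.2 | 78.6 → 79.0 | 77.7 → 77.9 |
| 0.5 | 94.6 → 95.2 | 92.5 → 93.6 | 76.7 → 79.0 | 76.3 → 77.7 |
| 0.8 | 93.0 → 94.9 | 91.3 → 94.6 | 74.9 → 79.3 | 72.3 → 78.2 |
| 1.0 | 91.9 → 95.3 | 89.1 → 94.1 | 72.6 → 80.0 | 69.2 → 78.6 |

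**The case against.** The strongest reply is that the harm is benign and may be nil. The T0 score absorbs much of any stable difference in level between countries, and no passage shows that a UK–Iran difference remains after that adjustment. The introduction's remark that "UK mothers made more mind-minded comments, while Indian mothers issued more instructions and positive comments" concerns India, not Iran, and is about levels. A different response to training by country is an interaction, which section 2.8.3 already examines. At f² = 0.15 power stays near 0.89 or above in every case computed. All of this stands, and it limits the size of the point.

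A second reply is that covariate lists are often left to the statistical analysis plan, that section 2.8.2 does not call baseline the only covariate, and that section 2.5 hints at further adjustment. This is weaker. The protocol is not silent: section 2.8.1 counts two predictors and names them, and section 2.8.2 repeats that structure. The hint in section 2.5 reaches no model in section 2.8.

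A reader might go further and infer that attachment scores from two age versions of the AISI are pooled, because section 2.5 says "This caregiver-report tool is specifically designed for two age groups: children aged 2 to 5 years and 6 to 12 years old" while enrolment covers ages 4 to 7. No passage says that two forms will be given, that they score differently, or that they will be combined. Age version is also not a stratification factor, so this argument would not reach it. Nor do the documents say that questionnaire language coincides with country: section 2.5 speaks of the preferred language for study information, and section 2.6 of the programme's language.

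**Conclusion.** The point holds as a modest efficiency fault in the stated T1 and T2 models. Its size runs from nothing, if country adds nothing beyond baseline, to intervals about 12% wider at a residual difference of 1.0 SD. It rests on an assumed range for δ, equal country samples, and a baseline–outcome correlation of 0.5 in the simulation. The type I figures below 5% also require arms balanced within country, which section 2.5 intends but does not secure with a stated block method.

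Two stronger readings should be resisted. One is that the treatment effect is biased or that false positives rise: randomisation within country rules out the first, and the calculations show type I error at or below about 5%. The other is that the plan both loses precision and misstates its standard errors. These are alternatives that depend on how allocation is done within country; they do not add up.

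**What to change.** In sections 2.8.1 to 2.8.3, specify every T1 and T2 model as outcome on group, T0 score and country, with country as a main effect. Keep the group-by-country term for the moderation analysis only. State the method of allocation within country, so that the reader can tell which of the two mechanisms would have applied. Bring the sentence in section 2.5 on confounders into line with this fixed covariate set.

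The cost is one degree of freedom and a line of text. Country is known for every participant at randomisation, and the required N does not change (55 for the group coefficient at f² = 0.15 and power 0.80, with two or three predictors).

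### The stated minimum of 89 does not follow from the stated power inputs, which give 55 or 68, and 100 recruits fall short of 89 at 15% attrition

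*Protocol*

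**What the plan says.** Protocol section 2.8.1 bases the sample size on G*Power 3.1 for linear regression "with two predictors: group assignment and baseline score". The inputs are given in full: "Assuming a medium effect size (f² = 0.15), an alpha level of 0.05, and a power of 0.80". The result is then reported: "the analysis indicated that a minimum sample size of 89 participants is required". The recruitment target follows: "To account for an expected attrition rate of approximately 10–15%, we plan to recruit 100 participants, with 50 participants in each group".

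Two other sections fix the setting. Section 2.8.2 makes the primary analysis a regression of the post-intervention score on group with the baseline score as covariate, so the quantity of interest is one coefficient. Section 2.8.4 sets two-tailed testing at 0.05. Section 2.8.1 does not say whether the power calculation tested the group coefficient alone or both predictors jointly.

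**The concern.** The section prints every input that the calculation needs, so the output can be checked, and it does not match. At least one printed figure (the power, the effect size or the 89) is therefore not the one that was used. This is not a detail that could wait for an analysis plan, because the protocol states both inputs and output and they disagree.

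At stake is how the result will be read. A null finding would be judged against 80% power for f² = 0.15, and that is not what 89 participants provide. The recruitment target also appears not to meet the minimum that it is meant to protect. A reader cannot tell which of the two numbers, the minimum or the attrition allowance, governs the target.

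**Working it through.** **Inputs.** From section 2.8.1: 2 predictors, f² = 0.15, alpha 0.05, power 0.80, minimum 89, attrition 10–15%, 100 recruits allocated 50:50. From section 2.8.4: two-tailed testing.

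**Formula.** Power for fixed-predictor multiple regression comes from the noncentral F distribution, with noncentrality λ = f² × N, numerator df u = number of predictors tested, and denominator df v = N − 2 − 1. Power = P(F(u, v; λ) > F crit(0.95; u, v)).

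**Step 1: try to reproduce 89.**

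| Test | N | λ = 0.15 × N | Critical F | Power |
|---|---|---|---|---|
| Group coefficient (u = 1) | 54 | 8.10 | 4.03 | 0.797 |
| Group coefficient (u = 1) | **55** | 8.25 | 4.03 | 0.805 |
| Both predictors (u = 2) | 67 | 10.05 | 3.14 | 0.798 |
| Both predictors (u = 2) | **68** | 10.20 | 3.14 | 0.804 |

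So the stated inputs give 55 or 68. Variants at alpha 0.05 and power 0.80 also fail to give 89:
- one-sided test of the group coefficient: 43
- λ = f² × v in place of f² × N: 58 (u = 1) or 71 (u = 2)
- joint test of 3, 4 or 5 predictors: 77, 85 or 92

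**Step 2: find what 89 corresponds to.** With u = 1, the required N is 55 at power 0.80, 73 at 0.90 and 89 at 0.95. With u = 2 it is 68, 88 and 107. The only exact match at alpha 0.05 and f² = 0.15 is the group coefficient at power 0.95. At N = 89, λ = 0.15 × 89 = 13.35, and power is 0.951 (u = 1) or 0.906 (u = 2). For 89 to give power 0.80, f² would have to be about 0.090 (u = 1) or 0.112 (u = 2).

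**Step 3: attrition.** The number to recruit is N/(1 − d), rounded up.
- Completers from 100 recruits: 100 × 0.90 = 90; 100 × 0.85 = 85.
- For 89 completers: 89/0.90 = 98.9, so 99 recruits; 89/0.85 = 104.7, so 105 recruits. With 100 recruits the largest tolerable loss is 1 − 89/100 = 11%.
- For 55 completers at 15%: 55/0.85 = 64.7, so 65 recruits. For 68: 68/0.85 = 80.0, so 80 recruits.

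**Step 4: what the planned sample delivers.** For 1:1 allocation the group indicator has variance 0.25. Hence f² = d²/4 and d = 2√f², where d is the adjusted between-group difference in residual SD units. For f² = 0.15, d = 2 × √0.15 = 0.77.

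| Completers | Power for f² = 0.15, u = 1 | Power for f² = 0.15, u = 2 | f² at 80% power, u = 1 | d in residual SD |
|---|---|---|---|---|
| 85 | 0.942 | 0.891 | 0.095 | 0.61 |
| 89 | 0.951 | 0.906 | 0.090 | 0.60 |
| 90 | 0.953 | 0.909 | 0.089 | 0.60 |

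**Step 5: why the test must be named.** Under the joint test, f² = 0.15 means R² = 0.15/1.15 = 0.130. A baseline–outcome correlation of √0.130 = 0.36 produces that with no treatment effect at all. Only the group-coefficient version speaks to the primary question in section 2.8.2.

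**The case against.** The strongest reply is that the error is on the safe side. With 85 completers, power for f² = 0.15 is 0.94 or 0.89, above the 0.80 claimed, so the planned sample meets its stated aim and only the word minimum is wrong. This stands, and it limits the consequence to a restatement. Equally, the attrition shortfall exists only against 89; at 10% loss 100 recruits suffice, and against 55 or 68 they suffice at 15% too. This also stands, but the section's own numbers still disagree at the top of its own range.

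A reader might go further in four ways that the documents do not support.

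- **That the trial is underpowered.** For the stated effect the calculation shows the reverse.
- **That power for a medium difference of 0.5 SD is only about 63%.** That figure (0.625 at 85 completers, 0.645 at 89) is for 0.5 residual SD. For 0.5 SD of the raw outcome, power depends on the baseline–outcome correlation r, which the protocol does not give. Dividing 0.5 by √(1 − r²) gives power of about 0.75–0.77 at an assumed r = 0.5 and 0.81–0.83 at an assumed r = 0.6.
- **That the within-group claim is false.** Section 2.8.1 speaks of "while maintaining enough power for within-group analyses" without defining those analyses. If they are paired pre–post comparisons in one arm of 42 to 50, power is 0.89–0.93 for an assumed standardised change of 0.5 and 0.72–0.79 for 0.4. The claim is undefined rather than shown to be wrong.
- **That the UK–Iran moderation analysis must be limited to estimation.** Section 2.8.1 claims no power for the interaction, and section 2.8.3 lists it as secondary with effect sizes and confidence intervals.

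**Conclusion.** Wrong as written, and should be fixed. The stated inputs give 55 (group coefficient) or 68 (both predictors), so 89 is 34 or 21 participants too high for power 0.80; the power at 89 is 0.95 or 0.91. Against the stated minimum, 100 recruits are four completers short at 15% loss (85 against 89) and five recruits short of the 105 needed.

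This rests on the standard noncentral-F calculation, two-sided alpha 0.05 and, for the conversion to residual SD, 1:1 allocation. That the power entered was 0.95 is a plausible explanation because it matches exactly, but the protocol does not confirm it. The design, the number recruited and the analysis are not called into question.

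**What to change.** Keep N = 100 and rewrite section 2.8.1:

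1. Name the test as the group coefficient adjusted for baseline, matching the primary analysis in section 2.8.2.
2. Replace 89 with the reproducible figure (55 for that test at power 0.80), or keep 89 and state the power or f² actually used.
3. Redo the attrition step as N/(1 − d), and show the number to recruit at both 10% and 15%.
4. State what the sample delivers, for example: *With 100 recruited and 10–15% attrition, 85 to 90 completers give about 94–95% power (two-sided 5%) for f² = 0.15, an adjusted between-group difference of 0.77 residual SD, and 80% power for a difference of about 0.60 residual SD (f² about 0.09).*

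The cost is protocol wording only. No participants, visits or analyses are added.
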